#### **PART ONE:**

Visit 1: (week 0) screening, 15 minute MRI scanning session, and then initiation of placebo

Visit 2: (week 2) evaluate clinical status, collect empty bottles and complete a 10 minute single MRI scan.

For Part one participants will receive compensation for completing visits 1 and 2. Compensation will be given to participants either at the end of each visit (if the amount is \$50 or under) or in the form of a check a few weeks later (if the amount is greater than \$50). Compensation is as follows:

Visit 1 (Scan 1): \$30.

Visit 2 (Scan 2): \$30.

#### **PART TWO:**

Visit 1: Pre-Screening: Medical history, physical exam, questionnaires

Visit 2: Screening: blood test, pregnancy test for women of childbearing potential, MRI scan

Visit 3: Randomization (within 2 weeks of screening): randomization and initiation of study drug/placebo and rescue medications (30 mg/day)

Visit 4: Interim Visit (week 1  $\pm$  3 days): evaluation of clinical status, increase dose of duloxetine/placebo to 60 mg/day

Visit 5: Interim Visit (week 6  $\pm$  7 days): evaluation of clinical status

Visit 6: Final Interim Visit (week 16  $\pm$  14 days): evaluation of clinical status, MRI scan, begin tapering the dose study drug/placebo over a 1 to 2 week period, collect empty bottles and unused rescue medication

Follow-up: Phone Call (week 18 at maximum): evaluation of clinical status, verify that the study drug/placebo was successfully stopped

Optional Visit: Interview (week 20 and beyond): ask questions about mood, pain, and health history, questionnaires

OA participants will receive compensation for completing visits 1, 2, 3, 4, 5, 6, and Optional. Healthy controls will receive compensation for visits 2, 6, and Optional. Compensation will be given to participants either at the end of each visit (if the amount is \$50 or under) or in the form of a check a few weeks later (if the amount is greater than \$50). Compensation is as follows:

Visit 1 (Pre-Screening): \$25 for OA; N/A for healthy controls

Visit 2 (Screening, with MRI): \$50 for all participants

Visit 3 (Randomization): \$25 for OA; N/A for healthy controls

Visit 4 (Interim): \$25 for OA; N/A for healthy controls

Visit 5 (Interim): \$25 for OA; N/A for healthy controls

Visit 6 (Final Interim, with MRI): \$50 for all participants

Follow-up (Phone Call): \$0 for OA; N/A for healthy controls

Optional Visit (Interview): \$25 for all participants

In addition, for both phases of the study, all participants will receive additional compensation for transportation and parking (if applicable), and this compensation is available for all visits (1 through 6, and optional if applicable). We will reimburse individuals up to \$20 in various travel expenses, such as CTA fares or driving costs, and we will validate their parking stickers if they park in the garage at [name] or at [name].

Brain image data collection and analysis is done under [name] supervision, which will be performed double blinded. Brain scan data will be transferred to [name]'s lab where the automated brain morphometric analyses are performed. We contrast brain morphology using a 2-way analysis of variance, factor one is group (patients treated with drug, with placebo, and healthy controls), and factor two is repeat measure time of scan. A secondary analysis will involve correlating brain regional changes to pain (VAS score from sf-MPQ) and the other questionnaire outcomes.

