Treatment begins at 30 mg once daily for 1 week, to allow patients to adjust to the medication before increasing to 60 mg once daily. Some patients may respond to the starting dose. There is no evidence that doses greater than 60 mg/day confer additional benefit, even in patients who do not respond to a 60 mg dose, and higher doses are associated with a higher rate of adverse reactions. Before discontinuing patients, a gradual reduction in the dose rather than abrupt cessation is recommended. Patients will take 30 mg once daily for 1 week before cessation.

Duloxetine should be swallowed whole and should not be chewed or crushed, nor should the capsule be opened and its contents sprinkled on food or mixed with liquids. All of these might affect the enteric coating. Duloxetine can be given without regard to meals.

Duloxetine's matching placebo pellets are filled into size 1 blue/blue capsugel shells. Overall ingredients: empty gelatin capsules and Nu-Pareil sugar spheres. The matching placebo has a stability of 60 months with minimum allowable storage temperature limits: 15 degrees C/max allowed 25 degrees C. Do not refrigerate or freeze. Route of administration is oral.

Duloxetine is commercially available. Duloxetine and its matching placebo is provided free of charge by the Neuroscience Division of Lilly USA, LLC.

Duloxetine contains a black box warning for Suicidality (suicidal thoughts and/or self-harmful behavior). There is an increased risk of suicidality in children, adolescents, and young adults with major depressive or other psychiatric disorders.

The most common adverse events (happening in more than 5 of 100 people) are:

- Nausea
- Constipation
- Diarrhea
- Decreased appetite
- Dry mouth
- Sweating or night sweats
- Dizziness
- Headache
- Tiredness

- Weakness
- Drowsiness

Less common adverse events (happening in at least 2 of 100 people) include the following:

- Vomiting
- Stomach and/or abdominal pain
- Increased urination
- Difficulty urinating
- Blurred vision
- Fast or irregular heartbeat
- Weight changes
- Tremors (uncontrollable shaking of a part of the body)
- Changes in sexual desire or ability (see section below)
- Yawning
- Hot flashes
- Acid reflux
- Fever
- Hoarseness or sore throat
- Muscle pain or cramps
- Flu-like symptoms
- Seasonal allergy-like symptoms
- Upper respiratory infection
- Change in taste
- Anxiety or agitation
- Tingling at the fingers or toes, or general differences in sensation
- Rash
- Hives
- Itching

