Rare adverse events (happening in 1 of 100 to 1 of 1000 people) include the following:

- Change in blood pressure
- Elevated liver enzymes

Serious adverse events that require immediate medical attention include the following:

- Unusual bruising or bleeding
- Pain in the upper right part of the stomach
- Swelling of the abdomen
- Yellowing of the skin or eyes
- Dark colored urine
- Extreme tiredness or weakness
- Confusion
- A combination of fever, sweating, confusion, and severe muscle stiffness
- Blisters or peeling skin
- Difficulty breathing or swallowing
- Swelling of the face, throat, tongue, lips, eyes hands, feet, ankles, or lower legs

- Worsening of depression-like symptoms
- Mania or hypomania (abnormally elevated mood, arousal, and/or energy-level)
- Withdrawal-like symptoms
- Serotonin syndrome (an adverse event that happens from taking certain combinations of medications; symptoms may involve increased heart rate, shivering, sweating, dilated pupils, intermittent tremor or twitching, changes in your reflexes, stiffness, and/or changes in bowels, blood pressure and body temperature)
- Neuroleptic malignant syndrome (similar to serotonin syndrome mentioned above, with the exception that neuroleptic malignant syndrome often involves a decrease in muscle tone and increased tiredness or weakness)
- Seizures
- Extrapyramidal symptoms (adverse events including extreme restlessness, involuntary movements, and uncontrollable speech)
- Damage to the liver
- High blood pressure resulting in organ damage
- Decreased level of sodium in the blood (could result in a coma)
- SIADH (inappropriate secretion of a natural hormone in the body that results in decreased sodium in the blood)
- Glaucoma
- Anaphylaxis (life-threatening allergic reaction)
- Stevens-Johnson syndrome (an adverse event that can lead to blistering of the mouth, palms, and/or soles)
- Erythema multiforme (a skin disorder due to an allergic reaction; may result in multiple circular, raised pink or red lesions)
- Exfoliative dermatitis (loss of the outer layer of skin)

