**PART TWO:**

- Visit 1: **Pre-Screening**. Medical history, physical examination, patient-reported outcome (PRO) battery of instruments (includes: a general health questionnaire (PHH), the short form of McGill Pain Questionnaire (sf-MPQ), WOMAC, and the Beck Depression Index (BDI)), the Pain detect questionnaire, and the Pain catastrophizing scale (PCS)
- Visit 2: **Screening/Baseline Scan**. Basic chemistry panel and complete blood count (CBC), pregnancy test for females of child-bearing potential, MRI scans
- Visit 3: **Randomization**. (Week 0) WOMAC, dispense Duloxetine/placebo (at 30mg/day) and rescue medications, collect information on concomitant medications
- Visit 4: **Interim Visit**. (Week 1 ± 3 days) Dispense drug/placebo (increase dose of duloxetine/placebo to 60 mg/day), WOMAC, collect AEs and concomitant medication information
- Visit 5: **Interim Visit**. (Week 6 ± 7 days) Dispense drug/placebo (same dose as in Visit 3), WOMAC, BDI, collect AEs and concomitant medication information
- Visit 6: **Interim Visit**. (Week 16 ± 14 days) Dispense drug/placebo (begin to gradually reduce dose via a down-titration of 30mg for 1 week), MRI scans, PRO battery, collect AEs and concomitant medication information; collect unused rescue medications and empty duloxetine/placebo bottles
- Follow-up: **Phone call**. (Week 18 maximum) Collect AEs and concomitant medication information, verify that participant has successfully stopped the drug/placebo

Optional: **Interview** (Week 20 and beyond): Ask a series of open-ended questions about participants' experiences with pain, overall mood and personality, and medical history; give questionnaires about personality and pain/medical beliefs and expectations

Control participants will only complete visits 2 and 6. More specifically, they will only complete the PHH (once during screening) and the BDI (at all visits). Urine dipstick pregnancy tests will only be done in healthy controls if the participant is a woman of child-bearing potential. No blood will be drawn. Control participants also have the choice of completing an optional visit at the very end of the study that involves answering questions in an open-ended interview and completing a set of new questionnaires that supplement this interview.

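### The week-18 limit on the closing phone call allows nothing for a late but permitted Visit 6, so the call can fall before the last taper dose

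*Protocol*

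**What the plan says.** The protocol gives the Part Two schedule twice: in the visit list under Study Design and again under Study Procedures (more detailed).

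- **Visit 6 and the taper.** Both places put Visit 6 at week 16 with a window of 14 days either way, and both start the taper there. The visit list says "begin tapering the dose study drug/placebo over a 1 to 2 week period". The detailed procedures say "Week 16 ± 14 days) Dispense drug/placebo (begin to gradually reduce dose via a down-titration of 30mg for 1 week". The Study Drug section agrees with the shorter form: "Patients will take 30 mg once daily for 1 week before cessation".
- **The call.** The visit list has "Phone Call (week 18 at maximum): evaluation of clinical status, verify that the study drug/placebo was successfully stopped". The detailed procedures have "Week 18 maximum) Collect AEs and concomitant medication information, verify that participant has successfully stopped the drug/placebo".
- **Time origin.** The detailed procedures label the randomization visit week 0, so weeks count from there and not from Visit 6.
- **After the call.** Only an elective contact remains: "Optional Visit: Interview (week 20 and beyond". No adverse event collection is listed for it.

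**The concern.** The call has a purpose that can be met only after dosing has ended: confirming that the patient has stopped. Its latest date is nevertheless fixed from randomization, while the start of the taper moves with the actual date of Visit 6. At the late end of the Visit 6 window the two rules cannot both be kept. A call inside the limit reaches a patient who is still taking capsules, and a call that waits for the end of the taper breaks the stated maximum.

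What is at stake is safety follow-up after withdrawal. The Study Drug section says "Before discontinuing patients, a gradual reduction in the dose rather than abrupt cessation is recommended", and it lists "Withdrawal-like symptoms" among the events that need immediate medical attention. The Safety Assessment section ties adverse event monitoring to clinical visits and the questionnaires, and Visit 6 is the last such visit. This call is therefore the only scheduled safety contact that could follow the last dose.

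**Working it through.** **Inputs.** Randomization is day 0 and week *w* is day 7*w*. Visit 6 is week 16 ± 14 days. The call limit is week 18. The taper length *L* is 7 days (Study Drug; detailed procedures) or 7 to 14 days (visit list).

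**Dates.** Visit 6: 16 × 7 = 112, so days 112 − 14 = 98 to 112 + 14 = 126. Call limit: 18 × 7 = 126.

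**Reproducing the plan's limit.** Taking the first taper dose on the day after Visit 6, the last dose is on day V6 + *L*. For an on-time Visit 6:
- 1 week: 112 + 7 = 119, which is 7 days inside the limit.
- 2 weeks: 112 + 14 = 126, exactly at the limit.

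Week 18 is thus what results from nominal week 16 plus the longest taper. Nothing is left for the + 14-day window.

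**Adding the window, week 18 read as day 126.** The taper outlasts the limit when V6 + *L* > 126:
- 1 week: V6 > 119, so days 120–126. Latest last dose 126 + 7 = 133, an overrun of 7 days.
- 2 weeks: V6 > 112, so days 113–126. Latest last dose 126 + 14 = 140, an overrun of 14 days.

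**Sensitivity to the two unstated conventions.** Week 18 might run to its last day, 126 + 6 = 132. The first taper dose might also be taken on the day of Visit 6, so that the last dose is on day V6 + *L* − 1.

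| Week 18 read as | First taper dose | 1-week taper: Visit 6 days in conflict (largest overrun) | 2-week taper: Visit 6 days in conflict (largest overrun) |
|---|---|---|---|
| day 126 | day after Visit 6 | 120–126 (7 days) | 113–126 (14 days) |
| day 126 | day of Visit 6 | 121–126 (6 days) | 114–126 (13 days) |
| up to day 132 | day after Visit 6 | 126 only (1 day) | 119–126 (8 days) |
| up to day 132 | day of Visit 6 | none (126 + 6 = 132) | 120–126 (7 days) |

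The 2-week conflict appears in every row. The 1-week conflict depends mainly on how week 18 is read.

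**The case against.** The best defence is that the schedule works at its nominal timing, as the reproduction shows. On this view the gap is a drafting slip, and staff would simply call a few days late because the call's purpose is plain. The taper itself, which is the real protection against withdrawal effects, is untouched by the limit. Monitoring is under direct physician supervision, which does not rule out an unscheduled contact. Most of this stands, and it is why the point is minor. It does not remove the point: the maximum is stated in both places, and the late call would depart from it.

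Four stronger readings are tempting, and the protocol does not support them.

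- **The taper length is contradictory.** A taper of one to two weeks includes one week, so a site using 30 mg for 1 week satisfies all three statements. The wording is loose, not contradictory.
- **Patients are stopped abruptly, or stopping can never be verified.** No patient loses the taper because of the limit, and verification fails only if a site keeps to the limit despite the call's stated aim.
- **Patients who leave before Visit 6 are unprotected.** The general rule in the Study Drug section already requires gradual reduction for them. The remaining dispensing and contact details are operational.
- **The conflicting days give a share of patients.** They are allowed calendar days. The protocol gives no distribution of visit dates.

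**Conclusion.** The point holds as a minor safety-schedule correction. The fixed week-18 maximum suits an on-time Visit 6 but fails at the late end of the permitted window. The extent depends on the reading of week 18 and on the taper length, and ranges from no conflict (1-week taper, both lenient conventions) to the last 14 days of the window (2-week taper, week 18 as day 126).

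The conclusion rests on counting weeks from randomization, as the detailed procedures do, and on the taper starting at Visit 6, as both schedules state. Withdrawal effects of the drug itself can concern only late completers in the duloxetine arm. The final MRI is done at Visit 6, where the taper only begins, so the primary and secondary imaging results are not touched.

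**What to change.** In the Part Two visit list and in the detailed procedures, replace the week-18 maximum with a call at a short stated interval after the last taper dose. An interval of 1 to 7 days is an assumption for the clinical team to confirm. The rule works for either taper length, so it need not settle which one is used.

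Resulting call dates, with the first taper dose on the day after Visit 6:

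- **1-week taper.** On-time Visit 6: last dose day 119, call days 120–126, still within the present limit. Latest Visit 6: last dose day 133, call days 134–140.
- **2-week taper.** On-time Visit 6: last dose day 126, call days 127–133. Latest Visit 6: last dose day 140, call days 141–147.

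The cost is a short amendment and a later call for some patients. With a 1-week taper only late completers are affected, by up to 140 − 126 = 14 days. With a 2-week taper the call can move by up to 147 − 126 = 21 days, and an on-time completer's call also passes day 126, by 1 to 7 days. The optional interview has no upper limit and can be booked after the call. Narrowing the Visit 6 window would also work, but it would restrict scheduling of the final scan, so moving the call is cheaper.

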The issue of atrophy due to pain in relation to changes due to aging warrants further clarification. In the 4 months of treatment all subjects should have atrophy due to aging, about  $2.5 \text{ cc} \times 0.3 = 0.75 \text{ cc}$ . On the other hand the OA cumulative atrophy over the years seems to be proportional to the number of years a given subject has had the condition. If we assume on average that the mean OA duration is 5 years, then the atrophy due to chronic pain should be about  $1.5 \text{ cc} \times 5 = 6.0 \text{ cc}$ . Therefore, in a subject where the OA pain completely disappears with treatment, that subject has the potential of exhibiting a reduction in atrophy of 6.0 cc minus the increased atrophy due to aging of 0.75 cc. Moreover, we assume that placebo responses will not induce reversal of atrophy because placebo mainly reflects attentional and motivational states of the person. There is likelihood that this assumption may not be true. Even in the latter case as we expect placebo to decrease pain less than the real drug treatment, we should still observe smaller changes in atrophy by placebo.

We consider the brain atrophy in chronic pain as an overall marker of the extent of peripheral, spinal cord, and brain reorganization a subject has developed with living and suffering with the condition. Animal models of chronic neuropathic and inflammatory pain repeatedly show that peripheral and spinal cord nociceptive transmission is dramatically changed, leading to

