### **Hypotheses:**

The primary hypothesis to be tested in the study is that subjects with chronic knee OA treated with Duloxetine over a four-month period will show decreased or arrested brain atrophy compared to subjects treated with placebo.

Secondary hypotheses are that in individual patients there will be a relationship between the magnitude of the analgesic effects of treatment and the magnitude of the change in brain atrophy. It is anticipated that there will be a correlation between pain relief by Duloxetine and changes in brain atrophy, whereas the degree of pain relief by placebo will not correlate with brain atrophy changes.

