For part two of the study, high-resolution anatomic brain images and functional brain scans are collected before and after four-months of treatment with duloxetine in 30 OA patients, in 30 OA patients who receive placebo, and in 25 healthy controls. Brain morphology is contrasted between these two time points, across the three groups, for overall neocortical gray matter volume and regional gray matter density changes. Pain relief, based on questionnaire outcomes and the MPQ's VAS, are then used as covariates in both patient groups to identify the effect size of magnitude of pain relief on restoration of brain grey matter. The procedures follow exactly our publications on the topic (Geha et al., *Neuron*. 2008; 60: 570. [name] et al., *J. Neuroscience* 24:10410, 2004).

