### ***Statistical Analysis***

As soon as participants' MRIs are collected they are transferred to [name]'s lab where again we check for quality. Final data analysis cannot begin until all the repeat brain scans are collected, where we then follow procedures that we have used in the past. The correlative analyses require also getting all the pain questionnaire and drug use outcomes at study completion.

All participants' scans will be run through a quality control pipeline. Those participants whose scans are returned by the pipeline as poor in quality (e.g, they may have a low signal-to-noise ratio or too much movement), and verified to be so by qualified personnel, will *not* be included in data analysis concerning how the brain changes under the influence of the study drug. However, these participants' questionnaire data, medical history, and pain reportings may still be used in data analysis concerning drug efficacy.

Brain morphometry analysis follows our published procedures (Geha et al., Neuron. 2008; 60: 570. [name] et al., J. Neuroscience 24:10410, 2004). Briefly, we use three approaches to compare brain anatomy between groups (primary hypothesis) and correlate brain anatomical parameters with pain relief in the treatment arm (secondary hypothesis). For all subjects we

calculate whole-brain gray matter volume for the neocortex, normalized by skull size, and corrected for sex and age confounds. In the first approach, this value is then contrasted between treatment and placebo groups, which test the primary hypothesis for the whole-brain. In a second analysis, we perform voxel-based morphometry (VBM) where we calculate gray matter density for each voxel of gray matter (3 mm^3, about 20,000 voxels/brain). The VBM results are corrected for whole-brain volume, age and sex, and then contrasted between the groups. This contrast indicates what specific brain regions have changed in gray matter density and in what direction. In the third approach, we subdivide the neocortical gray matter into 80 morphological sections (Brodmann areas), correct them for age, sex, and whole brain volume, and contrast them between the two groups.

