#### Sample Size Considerations:

Effect size: Given that the design is a within subject repeat measures analysis of variance, the overall variance should be about half of that we had originally anticipated. In fact, two recent studies were able to show significant restoration of grey matter in n=10 patients with such a design. However, in those two studies the pain relief was complete for many months. Here we expect a smaller decrease in pain (between 10-20mm on VAS scale from baseline) and, as a result, we have increased the sample size of the population treated with drug three times. Moreover, assuming that pain relief will be less in the placebo group, inclusion of this arm into the study should strengthen the power of the study. The healthy normal subjects tested at two equivalent time points is necessary to rule out that the observed results are scanner artifacts. In the normal subjects we specifically test that in the same time period and using the same scanner we observe no significant, or minimal increased atrophy (0.75 cc increase in atrophy, in the direction opposite of what we expect to see with drug treatment). Moreover, since we already have results regarding brain regions where atrophy is observed in OA, we can perform brain region-specific directed contrasts between the groups, if necessary. Overall, this design should give us enough power to test the primary and secondary hypotheses. It should be noted, however, that this is an exploratory study, and there is no statistical justification to our proposed sample size.

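### The one primary hypothesis has two different analyses, and neither names the duloxetine–placebo difference in change as the test

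*Protocol*

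**What the plan says.** Only the Protocol was available; no SAP was seen.

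- **Hypotheses.** Subjects "treated with Duloxetine over a four-month period will show decreased or arrested brain atrophy compared to subjects treated with placebo". This is a statement about change over time, compared between the two randomised arms.
- **Study Design, imaging paragraph after the Part Two visit list.** Brain morphology is analysed by a two-way analysis of variance in which "factor one is group (patients treated with drug, with placebo, and healthy controls), and factor two is repeat measure time of scan". The pain correlations that follow are called secondary, so the analysis of variance reads as the main one. The more detailed Study Procedures for Part Two agree: "Brain morphology is contrasted between these two time points, across the three groups".
- **Statistical Analysis.** The plan is to "calculate whole-brain gray matter volume for the neocortex, normalized by skull size, and corrected for sex and age confounds". In the first of three approaches, "this value is then contrasted between treatment and placebo groups, which test the primary hypothesis for the whole-brain". Healthy controls, a time factor, the scan used and the baseline scan are not mentioned.
- **Study Endpoints.** The primary endpoint is worded as volume and density; change appears only in the secondary endpoint.
- **Sample Size Considerations.** The reasoning rests on a within-subject repeated-measures design. The healthy controls are there to exclude scanner artefact, the expectation being that "we observe no significant, or minimal increased atrophy", with 0.75 cc given as the reference.
- **Randomization and Blinding Design.** Healthy controls are matched on age, gender and education. They are not randomised.
- **Anticipated Results.** Success is worded a third way: a rise from before to after treatment on duloxetine and none on placebo.

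**The concern.** A protocol may leave model details to a SAP, but here it gives two different main analyses for the same hypothesis and does not say which decides. One has three groups and a time factor; the other has two arms and no time factor.

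Each carries a risk if followed literally. The three-group interaction has two degrees of freedom, and one of the differences it picks up is osteoarthritis against healthy, which randomisation does not protect and which says nothing about the drug. The Protocol's own background makes such a difference plausible, since it attributes an extra 1.5 cc of loss per year to chronic pain. The two-arm contrast keeps to the right groups. If it is run on final volumes, though, it compares people with different brain sizes and gives up the within-subject precision on which the sample size reasoning rests.

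With both on the page, the choice among an omnibus F test, a volume contrast and a within-arm comparison can be made after the results are known.

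**Working it through.** **The plan's own figures.** The drug arm is three times the 10 patients of the two earlier studies: 3 × 10 = 30, hence 30 + 30 = 60 randomised, plus 25 healthy controls. No alpha, power, SD or effect in cc is tied to this, and the Protocol says that the sample size has no statistical justification. There is no power figure to reproduce. What follows measures what each reading would do.

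**Assumptions.** Two-sided alpha 0.05; complete data at 30/30/25; effects in SDs of change; scan-rescan correlation ρ from 0.5 to 0.95.

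**Reading 1: the omnibus group-by-time term decides.** With two scans this term equals a one-way analysis of variance on change, with 2 and 85 − 3 = 82 df. Let the two osteoarthritis arms change identically and the controls differ from both by d SD. The noncentrality is λ = d² × (60 × 25)/85 = 17.65 d².

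| d | λ | Probability of significance with no drug effect |
|---|---|---|
| 0 | 0 | 5% |
| 0.2 | 0.71 | 10.5% |
| 0.3 | 1.59 | 18% |
| 0.5 | 4.41 | 44% |
| 0.8 | 11.29 | 85% |

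To put d on the Protocol's scale: if neither arm reverses atrophy, the pain-related excess over four months is 1.5 × 4/12 = 0.5 cc. With an SD of change of 1, 2 or 5 cc, d is 0.5, 0.25 or 0.1, and the probability is 44%, 14% or 6%.

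**Reading 2: final volumes are contrasted between the arms.** Set the SD of a single-scan volume to 1. The SD of change is √(2(1 − ρ)), and the SD after baseline adjustment is √(1 − ρ²). Take the effect that gives the two-arm contrast of change 80% power with 30 per arm, which is 0.7356 SD of change. The noncentrality of each t test is effect/(SD × √(2/30)). The last column uses the normal approximation.

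| ρ | SD of change | Effect | Power, change | Power, final volume | Power, baseline-adjusted | n per arm for 80%, final volume |
|---|---|---|---|---|---|---|
| 0.50 | 1.000 | 0.736 | 80% | 80% | 90% | 30 |
| 0.75 | 0.707 | 0.520 | 80% | 51% | 85% | 59 |
| 0.90 | 0.447 | 0.329 | 80% | 24% | 82% | 146 |
| 0.95 | 0.316 | 0.233 | 80% | 14% | 81% | 291 |

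The sample size section expects the within-subject design to halve the variance. If that is relative to a single-scan comparison, 2(1 − ρ) = 0.5 gives ρ = 0.75, the row with 51%.

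**Does the omnibus test also lose power?** At a true drug effect of 0.74 SD of change, the two-arm contrast has 80.5%. The omnibus test has 71% if controls lie midway between the arms and 82.5% if they change like either arm. There is no general loss.

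**The case against.** The strongest reply is that the Protocol can be read sensibly. The Statistical Analysis section assigns the primary hypothesis to treatment against placebo, without healthy controls, and nowhere does the Protocol say that an omnibus F test decides it. The group-by-time term contains the drug–placebo difference in change as a one-df contrast. A final-volume contrast between randomised arms is valid, only inefficient. Change is clearly the intention elsewhere: the background speaks of a within-subject contrast, the procedures compare two time points, and the analysis waits for the repeat scans. The study also calls itself exploratory.

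Most of this stands, and it limits the point. A reader might infer that neither analysis tests the hypothesis; for the reasons just given, that goes too far. Three further inferences also fail:

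- That the three-group test generally costs power. This depends on where the controls fall. The Protocol expects little change in controls and no significant change on placebo, so they would lie close together, where nothing is lost.
- That osteoarthritis duration and site must be covariates. Background and Rationale does say that cumulative atrophy "seems to be proportional to the number of years a given subject has had the condition", but the entry criterion only sets a 12-month minimum. No section says that years of disease are recorded as an analysis variable, and leaving out a prognostic covariate does not bias a randomised comparison.
- That the control check rests on non-significance alone. The same sentence gives 0.75 cc as a reference.

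What the reply does not remove is the contradiction. No section reconciles the two descriptions or names the contrast of interest. The only directed contrasts offered are region-specific and conditional on need. The exploratory label excuses the sample size, not two different tests of one stated hypothesis.

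**Conclusion.** The point holds as an unreconciled inconsistency about the primary test. The hypothesis is a difference in change between two randomised arms. One description adds non-randomised controls and names no contrast; the other has the right arms but does not say which scan is used or how baseline enters.

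The consequence depends on the reading taken. Under the omnibus reading, a significant result need not concern the drug: about 10% to 44% of trials with no drug effect, for control differences of 0.2 to 0.5 SD of change. Under the literal final-volume reading, 80% power falls to between 51% and 14% for correlations of 0.75 to 0.95, while at 0.5 nothing is lost. If the intended analysis is the drug–placebo contrast of change, neither consequence arises, and only the wording is at fault.

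Every SD, difference and correlation here is an assumption, because the Protocol states none. The correlation that matters is the one left after correction for skull size, age and sex, which may be lower than the raw one. No figure in the Protocol is shown to be wrong by this point.

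**What to change.** State one primary analysis and use the same wording in Study Design, Study Procedures, Study Endpoints, Statistical Analysis and Anticipated Results:

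- The duloxetine–placebo difference in Visit 6 skull-normalised neocortical gray matter volume, in the two randomised arms only, adjusted for baseline volume, age and sex, with a 95% CI. The difference in change is an acceptable alternative aimed at the same quantity: at ρ = 0.90 its variance is 2(1 − 0.90) = 0.20 of the single-scan variance, against 1 − 0.90² = 0.19 after baseline adjustment.
- Healthy controls outside the primary model, as the scanner-drift check: their mean change with a 95% CI, set against the expected 0.75 cc ageing loss.
- The three-group by time analysis, if kept, labelled descriptive.

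The cost is wording in the Protocol and any SAP, settled before unblinding. Both scans are already scheduled, and the Protocol already plans to correct for age and sex, so no new data are needed.
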